## Abstract

**Background:**

Rates of obesity worldwide continue to increase and are associated with myriad health risks and socioeconomic burdens. Exercise is a traditional treatment for adults with obesity to increase physical activity levels, improve cardiorespiratory fitness, and reduce cardiometabolic risk. However, many people living with obesity do not engage in enough physical activity to achieve health benefits and often cite a perceived lack of time, lack of access to equipment, and stigma as barriers. “Exercise snacks” are short (~1 min) isolated bouts of vigorous exercise performed sporadically throughout the day that may be a viable strategy to improve fitness and cardiometabolic health. It is unknown whether exercise snacks are a feasible option in the real world for people living with obesity.

**Objective:**

This study aims to conduct a pilot randomized clinical trial (RCT) to determine the feasibility and preliminary efficacy of a 12-week smartphone app–supported exercise snacks intervention with behavior change counseling for improving cardiorespiratory fitness and other indices of cardiometabolic health in previously inactive adults living with obesity.

**Methods:**

A 2-site, parallel arm, RCT will be conducted in Kelowna and Hamilton, Canada. Eighty inactive adults living with obesity will be randomized to an exercise snacks or stretching/mobility exercise comparator group for 12 weeks. The former will complete 4 × 1-minute bouts of vigorous exercise at least 5 days per week, and the latter will perform mobility or stretching exercises using the same schedule. Interventions will be delivered through a customized smartphone mobile app and will be tailored to the participants’ schedules via onboarding counseling sessions, with ongoing telephone check-in call support at weeks 1, 2, 4, and 8. This pilot RCT will focus on feasibility as reflected by rates of recruitment, adherence, and dropout. We will also assess cardiorespiratory fitness, anthropometric markers, and routine blood health markers (eg, glucose, insulin) at baseline and postintervention.

**Results:**

This study is funded through the Heart & Stroke Foundation of Canada Grants-in-Aid program (2024/2025). Recruitment began on July 18, 2025 (Kelowna) and in November 2025 (Hamilton). As of March 31, 2026, we have enrolled 65 participants (University of British Columbia Okanagan, n=51; McMaster University, n=14). Data analysis will begin once all enrolled participants have completed the trial, and we expect to publish the results of the trial in winter 2027.

**Conclusions:**

This study will test an RCT protocol, provide evidence on the feasibility of exercise snacks in inactive adults living with obesity, and report preliminary effect size estimates for their ability to improve cardiometabolic health.

## Introduction

### Background

Obesity represents one of the largest health care challenges to Canadian society. In 2022, approximately 30% of Canadian adults were living with obesity [1], costing Canada approximately $28 billion annually in health care costs and lost productivity [2]. Obesity contributes to the development of a variety of cardiometabolic diseases such as cardiovascular disease, cancer, and type 2 diabetes [3]. While exercise represents a nonpharmacological treatment for many of the comorbidities associated with obesity, many adults living with obesity are insufficiently active [4,5]. Given the individual, societal, and economic burdens of obesity and its associated comorbidities, strategies targeting multiple aspects of cardiometabolic health are needed to help combat the obesity epidemic.

Chronic exercise is an established strategy to improve cardiorespiratory fitness [6-8], reduce blood pressure [9-11], as well as reduce adiposity and improve body composition [12-14] in adults living with overweight or obesity. Integrating small amounts of physical activity can have important implications as even modest improvements in fitness are associated with meaningful reductions in all-cause and cardiovascular disease mortality risk [15,16]. Despite these potential benefits, many people living with obesity are insufficiently active to achieve health benefits [4,5] and commonly cite a perceived lack of time and lack of access to equipment or facilities as barriers to physical activity [17]. Additionally, adults living with obesity face substantial stigma, which may limit motivation to participate in traditional exercise options (eg, fitness classes, exercising in public) [18,19]. Considering the deleterious health effects of obesity and low levels of physical activity in this population, there is an urgent need for time-efficient and accessible exercise strategies that can help individuals living with obesity become more physically active, improve their fitness, and reduce their risk of developing cardiometabolic diseases.

“Exercise snacks” are a practical and accessible form of physical activity that could improve cardiorespiratory fitness and cardiometabolic health in this population. Exercise snacks have been defined as isolated ≤1-minute bouts of vigorous exercise performed periodically throughout the day without the need for specialized equipment [20]. This approach to exercise may simultaneously promote engagement in vigorous physical activity and simultaneously interrupt sitting time [20,21]. Laboratory studies demonstrate that exercise snacks are well tolerated in inactive adults [22-24], including those living with obesity [25], and can improve cardiorespiratory fitness by approximately 4% to 5% compared to control or baseline [23,24]. Additionally, a laboratory-based study reported that on days exercise snacks are performed, adults living with obesity have lower postprandial plasma insulin and free-fatty acid levels compared to a day when they remain sedentary [25], highlighting the potential cardiometabolic benefits of brief bouts of exercise interspersed throughout the day. A recent 12-week randomized clinical trial (RCT) demonstrated that exercise snacks delivered through an online platform and mobile app were feasible to complete in the real world (ie, at home or work) with high enjoyment ratings in healthy (not living with obesity) but inactive adults [26]. The viability of exercise snacks to improve physical activity levels and cardiorespiratory fitness, while interrupting sedentary time and obesity-related risk factors, in people living with obesity is unknown. The proposed project will determine whether exercise snacks can be used as an approach to deliver the therapeutic benefits of physical activity in people living with obesity.

### Study Objectives

This study aims to conduct an RCT to determine the feasibility and preliminary efficacy of a 12-week smartphone app–supported exercise snacks intervention with behavior change counseling for improving cardiorespiratory fitness and other indices of cardiometabolic health in previously inactive adults living with obesity. Our specific aims are as follows:

Determine the proportion of individuals living with obesity who are eligible to participate, enroll in the trial, and are retained at 12-week postintervention testingMeasure adherence, cardiorespiratory fitness, plasma glucose, and insulin to inform effect size estimates for a future definitive RCTEvaluate the acceptability of the intervention by identifying barriers and facilitators and the most effective and ineffective aspects of the intervention to optimize the delivery of a future RCT

## Methods

### Trial Design

This pilot RCT will involve a parallel-arm design where participants are randomized (1:1 allocation ratio stratified by sex and site) into an exercise snacks or stretching/mobility exercise comparator group for 12 weeks (Figure 1). Target enrollment is 80 participants recruited from Kelowna, BC (University of British Columbia [UBC] Okanagan), and Hamilton, ON (McMaster University), and their surrounding areas using online advertisements supported by a recruitment service agency (Wayturn, Mariefred, Sweden). At each site, potential participants’ contact information is provided to the research team, which will initiate contact to schedule a screening call to determine eligibility before booking the first baseline study visit. Interventions will be delivered at home or work via a custom study mobile app and individualized via onboarding telephone exercise counseling sessions to develop an action plan for incorporating exercise snacks or stretching exercises into participants’ daily routines. Primary outcomes focused on feasibility will be assessed over the course of the intervention, and secondary outcomes focused on efficacy will be assessed at baseline and following the 12-week intervention. A flow diagram for the trial is presented in Figure 1.

**Figure 1. F1:**
[figure not shown]
Study timeline. This pilot randomized clinical trial (RCT) will involve a parallel-arm design where participants are randomized into an exercise snacks or stretching/mobility exercise comparator group for 12 weeks. Eighty inactive adults living with obesity will be recruited from Kelowna, BC, and Hamilton, ON. Once deemed eligible via phone screening, participants will report to the laboratory for their first visit, where informed consent will be obtained, entry questionnaires completed, and eligibility confirmed. Participants will wear an accelerometer for 7 days and report back to the laboratory for the second visit, where all baseline measurements will be conducted; the participants will be randomized, and they will undergo a behavior counseling session. Afterward, the participants will begin the 12-week intervention and have check-in calls at weeks 1, 2, 4, and 8. Participants will wear the accelerometer for 7 days during the last week of the intervention and then report back to the laboratory for the postintervention testing, where all outcomes will be reassessed.

### Ethical Considerations

During visit 1, informed consent will be obtained (by the lead trainee at each site) before any trial-related procedures are carried out, eligibility will be confirmed, and participants will be familiarized with the study procedures. During visits 2 and 3, secondary outcomes will be assessed. The protocol was approved by the UBC Clinical Research Ethics Board (H21-03417; version 10) and the Hamilton Integrated Research Ethics Board (19021; version 4) and was registered on ClinicalTrials.gov (NCT06924346) on July 17, 2025, before any participants were enrolled. This draft is version 5 of this protocol. Should a need arise that requires an amendment to the study protocol, the research team will gather to discuss the potential changes. If substantial amendments are required, they will be submitted to the site-specific ethics boards, and once approved, they will be implemented. The study is sponsored by the UBC Okanagan and funded by the Heart & Stroke Foundation of Canada (G-24‐0036465). The sponsor and the funder have no influence on study design, collection, management, analysis, and interpretation of data, writing of the report, and the decision to submit for publication. The data will be collected and stored in accordance with UBC Clinical Research Ethics Board and Hamilton Integrated Research Ethics Board policies. All data will be entered electronically, and files will be stored on secure servers at both sites for 5 years according to the policies outlined in each site’s respective ethics board. The data management team will consist of the principal investigators (PIs) at each site, the lead trainee at each site, and the trial statistician, who will meet monthly. The PI will be responsible for the integrity of the data stored on a secured Microsoft Teams channel, with the lead trainee and trial statistician responsible for database cleaning and locking. Only members of the research team will have access to the data during and after the completion of the study.

### Participants and Eligibility Criteria

Eligible participants will be living with obesity, currently inactive, and aged between 35 and 64 years. Potentially eligible participants will be contacted via phone or email to complete the eligibility screening, which includes a medical history, self-reported anthropometric measurements, current physical activity behavior, and details of current medications. Once participants have consented to participate, they will be assigned a deidentified code, and all data will be linked to their deidentified code rather than identifying information (eg, name, date of birth, email address). Informed consent forms and any other data collection sheets that contain identifying information will be stored separately from deidentified data.

There are no formal guidelines for determining sample size for a pilot trial, but published simulations suggest that 35 participants per group are appropriate for estimating the pooled SD for normally distributed variables to allow for accurate effect size estimates on outcomes [27]. This sample size is in line with the median sample size for pilot (n=30) and feasibility (n=36) trials in a published audit of registered pilot or feasibility trials [28]. In line with this, we will aim to recruit 40 participants per group (80 participants in total). Detailed inclusion and exclusion criteria are described in Textbox 1; participants will first be screened for these criteria during a screening phone call followed by confirmation during the first laboratory visit (Figure 2).

Textbox 1.Detailed inclusion and exclusion criteria.
**Inclusion criteria**
Aged 35‐64 yearsEngaging in ≤150 minutes of moderate-vigorous physical activity per week assessed using the Canadian Society for Exercise Physiology (CSEP) Get Active Questionnaire.BMI ≥30 kg/m^2^ (≥27.5 for participants who self-identify as being of Asian or Southeast Asian origin).Waist circumference ≥88 cm for female and 102 cm for male participants (≥80 cm for female and ≥90 cm for male participants who self-identify as being of Asian or Southeast Asian origin).Not currently diagnosed with a cardiometabolic disease (eg, coronary artery disease, stroke, diabetes, nonalcoholic fatty liver disease).Taking ≤2 commonly prescribed medications for the prevention of cardiometabolic diseases (eg, statins, antihypertensives, glucagon-like peptide-1 receptor agonists).Cleared to engage in physical activity using the CSEP Get Active Questionnaire and, if applicable, consultation with a health care provider or certified exercise physiologist.Not a current smoker.Access to a computer, tablet, or smartphone for intervention delivery and tracking.Able to read and write in English.
**Exclusion criteria**
A chronic musculoskeletal condition or recent (within 2 years) cardiovascular event preventing participation in exercise.Lack of internet access.Angina upon exertion assessed by the Rose Angina Questionnaire.Prescribed beta-blockers that can compromise the validity of heart rate measurements during exercise testing.Have a scheduled surgical procedure within the next 3‐4 months that would prevent exercise participation.Currently participating in another clinical trial that interferes with the study procedures.Currently pregnant or planning on becoming pregnant during the intervention (ie, within the next 4 months).

**Figure 2. F2:**
[figure not shown]
Trial flow diagram that will be used to determine the number of participants expressing interest, the number of participants who sign the informed consent form and complete the initial screening, the number of participants randomized to each group, the number of participants who complete the intervention, as well as the number of participants who are included in the final analysis. At all steps, the number of participants who are excluded or withdraw from the study will be recorded.

### Randomization and Blinding

The randomization of participants will occur during the second baseline testing visit after the collection of baseline measures. Participants will be randomized using a 1:1 allocation ratio with variable permuted block sizes (stratified by sex and site) through the web-based platform REDCap (Research Electronic Data Capture) tools hosted at the UBC (Research Electronic Data Capture, Nashville, USA) [29,30]. A researcher not involved in the project created the randomization sequence. When a new participant completes baseline testing and is ready for randomization, the participant’s sex and site will be entered by the researcher into REDCap, which will display the randomization (exercise snacks, stretching exercise comparator) for that participant. Due to the nature of the intervention, blinding of the participants or the researchers delivering the intervention is not possible.

### Interventions

Participants in both groups will be instructed to complete at least 4 × 1-minute exercise bouts periodically throughout the day on at least 5 days per week (ie, a minimum prescription of 20 minutes of vigorous activity via 1-minute exercise snacks per week). This aligns with recent updates to the World Health Organization Guidelines on Physical Activity and Sedentary Behavior, which recognize the health benefits of short activity bouts [31], and falls within Canada’s 24-hour Movement Guidelines for Adults recommendation to break up long periods of sitting as much as possible [32]. The timing of exercise bouts will be tailored to participants’ daily schedules, and the complexity of movements will be customized to participants’ preferences and abilities. The interventions will be delivered through the Seven Movements app (Seven Movements), which will provide daily reminders to perform the exercise bouts. Seven Movements developed this app for the study but had no involvement in the study design and will not be involved in the analysis or reporting of the results. Notifications through the app will be customized to each participant’s schedule during the onboarding session completed at the baseline visit and adjusted during subsequent telephone check-ins if needed. Instructional videos prepared by the research team will be provided for each movement to ensure the participants are performing the exercise correctly and safely. The videos will provide brief (10 s) instructions and show individuals completing the exercises along with a 1-minute timer with brief audio encouragement throughout. In the app, participants will be able to log the number of daily exercise bouts completed, as well as the corresponding perceived effort (Borg CR-10 scale [33]) and enjoyment (Exercise Enjoyment Scale [34]).

### Exercise Snacks Group

Exercises for the exercise snacks group are designed to increase heart rate over the course of 1 minute and include running on the spot, speed squat, change of direction run, box run, shadow box chair squat, jumping jack, stair climb, twisty jack, side shuffle, and alternating lunge. Participants in this group will be instructed to complete the 1-minute exercise bouts at an intensity that would elicit a Borg Category-Ratio-10 rating of perceived exertion (RPE) value of ≥7. During visit 2, participants will complete 2 familiarization exercises to ensure they understand the required intensity to elicit an RPE value of ≥7.

### Stretching Exercise Comparator Group

Exercises for the stretching/mobility exercise comparator group are mobility and stretching-based and designed not to raise heart rate. Movements include shoulder stretch, wall-chest stretch, quadriceps stretch, wall-calf stretch, cat-cow, seated glute stretch, hamstring stretch, high-lunge arm-raise, side bend, and kneeling hip stretch. Participants in this group will be instructed to complete the 1-minute exercise bouts at an intensity that would elicit a BORG CR-10 RPE value of 2‐3. This was selected as the most appropriate control group in attempts to balance randomization expectations, retention, and ethical considerations compared to a true “no exercise” control.

### Onboarding and Check-in Calls

After participants are randomized during baseline visit 2, they will meet with a research assistant for an onboarding session to further individualize the intervention and promote adherence. During the onboarding session, each participant will be provided with more detailed instructions on how to complete the exercise bouts using the smartphone app and help customize the exercise bouts prescription to fit their daily schedules (eg, choosing days of the week and times to do the exercise bouts). Using motivational interviewing techniques designed to overcome anticipated barriers and increase adherence [35-37], the research assistants facilitating these sessions will use a standardized brief action planning [38,39] interview guide to codevelop individual plans with each participant.

Participants will meet with research assistants for telephone check-in calls at the end of weeks 1, 2, 4, and 8. The check-in calls at the end of weeks 1 and 2 will focus on troubleshooting any issues experienced with the smartphone app, providing modifications for exercises, and checking if participants’ adherence and RPE match their group’s prescription. If participants request modifications for exercises, these instances will be recorded in a check-in call summary document that summarizes the main points discussed with the participant. Check-in calls at weeks 4 and 8 will be used to assess progress and goals developed during the onboarding session, provide continued support throughout the trial, and make any modifications to the exercise plan.

### Outcome Measures

Primary and secondary outcome measures are listed in Textbox 2 and then described in full detail in the text. Primary outcomes are all related to feasibility and collected over the duration of the intervention. Secondary outcomes are related preliminary to efficacy and are collected at baseline and postintervention.

Textbox 2.Primary and secondary outcomes.
**Primary outcomes**
The number of individuals eligible to participate in the trial, the number of participants approached, and reasoning for not joining the study.The number of eligible participants who enroll in the study.The number and percentage of participants retained after the 12-week intervention, as well as the number of participants who drop-out and reasons.The number of 1-minute exercise bouts performed during the 12-week intervention.
**Secondary outcomes**
Cardiorespiratory fitness estimated from walking treadmill test.Lower body muscular endurance assessed using sit-to-stand test.Upper body maximal strength assessed using hand-grip dynamometer.Waist circumference.Weight.BMI.Fasting plasma glucose.Fasting plasma insulin.Systolic blood pressure.Diastolic blood pressure.Physical activity estimated using accelerometry.

Feasibility outcomes will include the number of participants who are eligible to participate, the number of participants who enroll, the number of participants who are retained at 12-week postintervention testing, as well as the number of 1-minute exercise bouts completed during the intervention. The proportion of participants contacted, screened, and enrolled in the intervention will be recorded, as well as the number of eligible participants who chose not to participate (and reasons why). Adherence will be determined by summing the total number of 1-minute exercise bouts completed during the intervention. The primary adherence outcome will be app-reported adherence, and this will be supplemented (where needed) with participant self-report (via weekly REDCap surveys) for participants who choose to perform movement breaks outside of the app. We will define high, moderate, and low adherence as completing >70%, 50% to 69%, or <50% of the prescribed intervention, respectively. Feasibility is defined as >70% of the participants completing at least 67% of the exercise bouts (ie, >13 weekly bouts) on at least 8 out of 12 weeks.

A modified Balke walking treadmill test will be used to estimate cardiorespiratory fitness [40-42]. To begin, participants will complete a 3-minute warm-up at 3.2 km/h and 0% incline on a motorized treadmill. Upon the completion of the warm-up, the test will begin, and the speed will be increased to 5.3 km/h where it will remain for the remainder of the test, with 1% increases in grade every minute until volitional fatigue. Participants will be familiarized with this test during the first baseline testing visit, and if the test duration is ≤7 minutes, ≥13 minutes, or ≥15 minutes, then the speed for all subsequent tests (visits 2 and 3) will be adjusted to 4.5, 6.1, or 6.9 km/h, respectively. The speed and maximal grade attained on the test will be used to estimate cardiorespiratory fitness using the calculation below [43].

$${VO}_{2\max}\;(mL\;kg^{-1}\;min^{-1})=speed\;(m\;min^{-1})\times \left(0.17+(fractional\;grade\times 0.79)\right)+3.5$$

Lower body muscular endurance will be assessed using the 30-second sit-to-stand test. Participants will start in a seated position with their feet flat on the floor at shoulder width and their hands on their shoulders. Participants will be instructed to fully stand up and sit down as many times as possible within the 30-second period. A stopwatch will be used to record the time, and the number of repetitions will be counted by 2 researchers. If the participant has completed a full stand from the sitting position when the time has expired, the final repetition will be counted in the total.

Upper body maximal strength will be assessed using a hand-grip dynamometer. The grip on the dynamometer will be adjusted so that the participant can comfortably grip the device and their fingers comfortably fit under the handle at the second knuckle. Participants will be asked to hold the dynamometer in line with the forearm, at thigh height, away from the body. Grip strength will be measured twice on both hands, alternating after each attempt. If a difference of more than 5 kg is recorded between 2 trials (for the same hand), a third trial will be conducted. The maximum score for each hand measured to the nearest kilogram will be recorded and combined for a total score.

Waist circumference will be measured using a tape measure (calibrated at regular intervals) at the level of the superior lateral aspect of the iliac crest. Participants will be asked to lift their shirts to expose their abdomen and landmark the superior lateral aspect of the iliac crest. The assessor will place the tape measure around the landmarked location, and after ensuring it is level around the abdomen, the measurement to the nearest 0.5 cm at the end of expiration will be recorded. The average of 2 measurements will be recorded. If participants are not comfortable exposing their abdomen, the measurement will be conducted over the shirt and repeated at post-testing. Weight will be measured to the nearest 0.1 kg using a mechanical scale, and participants will be asked to remove their shoes, remove any baggy clothing, and empty their pockets before stepping on the scale. Height will be measured to the nearest millimeter using a stadiometer using the same instructions as the weight measurement. Height and weight will be used to calculate BMI, which will be expressed as weight in kilograms divided by height in meters squared.

Fasted blood samples will be obtained from an antecubital vein for the measurement of plasma glucose and plasma insulin. Once the samples have been collected, they will be centrifuged, and plasma aliquots will be stored at −80 °C. Plasma glucose and insulin will be analyzed using commercially available assays (Chrystal Chem). Homeostatic model assessment of insulin resistance (HOMA-IR) will be calculated using the calculation below [44].

$$HOMA\text{-}IR=\frac{fasting\;insulin\;(\mu U/mL)\times fasting\;glucose\;(mmol/L)}{22.5}$$

Blood pressure will be measured on the left arm using an automated blood pressure monitor. Prior to the measurement, participants are encouraged to use the bathroom and void their bladder. Blood pressure will be measured after 5 minutes of quiet seated rest. Three measurements will be taken with 1-minute rest in between measurements, and additional measurements will be taken, if necessary, until 3 measurements are obtained where systolic blood pressure is ≤5 mm Hg of one another. During the 5 minutes of quiet seated rest and while measurements are being conducted, the participant will be asked to sit motionless with their feet together, back against the backrest of the chair, and their left arm resting on the table beside them.

Physical activity will be assessed using activPAL4 accelerometers (Pal Technologies Ltd). The devices will be initialized using PALconnect (v9.1.2.168) to collect triaxial acceleration data at 20 Hz with a dynamic range of ±4 g and will be worn on the midline anterior aspect of the nondominant thigh for 7 consecutive days at baseline and week 12. The devices will be waterproofed and secured with a transparent film dressing, and participants will be instructed to remove and reattach the device only if the adhesive loosens. Upon retrieval, raw .datx files will be downloaded using PALconnect (v9.1.2.168), processed using PALbatch (v9.1.0.77), and exported as uncompressed, uncalibrated .csv files in g format to enable further processing. Raw acceleration data will be processed using the open-source R package GGIR (v3.2.9) using default signal-processing procedures, including automatic calibration using local gravity [45], nonwear detection, identification of sustained abnormal acceleration, and calculation of 5-second ENMO (Euclidean Norm Minus One) values [46]. From GGIR day-summary outputs, average acceleration (mg), intensity gradient, most active “x” minutes metrics ranging from M1 to M10, and time accumulated in 50 mg incremental acceleration bins from 0 to >400 mg will be extracted to characterize overall activity volume and the distribution of activity intensity across the 24-hour day [47,48]. Participants will be included if they provide at least 3 valid days of data, defined by ≥75% device alignment [49], ≥16 hours of valid wear time, and a calibration error <10 mg [46].

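### The adherence sum and the weekly feasibility rule ignore how bouts are spread over days, so massed sessions can count as feasible exercise snacks

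*Protocol article*

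**What the plan says.** All references are to the Protocol article.

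- **What an exercise snack is** (Background): "isolated ≤1-minute bouts of vigorous exercise performed periodically throughout the day".
- **What is prescribed, in both arms** (Interventions): "at least 4 × 1-minute exercise bouts periodically throughout the day on at least 5 days per week". The same sentence restates this as a weekly minimum of 20 minutes.
- **Primary outcome** (Textbox 2): "The number of 1-minute exercise bouts performed during the 12-week intervention".
- **Adherence measure** (Outcome Measures): "Adherence will be determined by summing the total number of 1-minute exercise bouts completed during the intervention".
- **Adherence bands** (Outcome Measures): "We will define high, moderate, and low adherence as completing >70%, 50% to 69%, or <50% of the prescribed intervention, respectively".
- **Feasibility rule** (Outcome Measures; the quote breaks off before the total of 12 weeks): "Feasibility is defined as >70% of the participants completing at least 67% of the exercise bouts (ie, >13 weekly bouts) on at least 8 out".
- **Data source**: the app is primary. In it, "participants will be able to log the number of daily exercise bouts completed" (Interventions). Where needed it is supplemented by "participant self-report (via weekly REDCap surveys) for participants who choose to perform movement breaks outside of the app" (Outcome Measures).

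No stated rule limits the bouts that count on one day, requires a number of active days, or asks for spacing between bouts.

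**The concern.** The intervention is defined by its distribution: single short bouts, several a day, on most days. The scoring keeps the volume and drops the distribution. Extra bouts on one day fully offset days on which nothing was done, so a weekend interval workout and a week of spread-out bouts can receive the same score.

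This bears on a primary outcome. The Discussion says the feasibility outcomes serve to decide whether this population can adhere before a larger trial is run, and the Introduction motivates the format by lack of time. If the rule is met partly by massed sessions, the result supports a weekly volume of vigorous minutes and not the format under test. The Discussion also reasons that the stretching comparator isolates vigorous intensity because both arms interrupt sitting. A bout total cannot show that either arm did so on most days.

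**Working it through.** **1. Reproduce the stated threshold.** Prescribed bouts per week: 4 × 5 = 20; over 12 weeks: 20 × 12 = 240. Then 0.67 × 20 = 13.4, so the smallest whole count is 14 (14/20 = 70%; 13/20 = 65%). This agrees with the article's more than 13.

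**2. Score weekly patterns.** The stated rule sums all bouts. The comparison credits at most 4 bouts per day, Σ min(4, bouts on that day). The 4 is the prescribed daily minimum and serves here only as a scoring device.

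| Bouts on active days | Total | Stated rule (≥14) | Credited, up to 4 per day | Same rule on credited bouts |
|---|---|---|---|---|
| 14 | 14 | met | 4 | not met |
| 7 + 7 | 14 | met | 8 | not met |
| 5 + 5 + 4 | 14 | met | 12 | not met |
| 5 + 5 + 5 | 15 | met | 12 | not met |
| 4 + 4 + 4 + 2 | 14 | met | 14 | met |
| 4 + 4 + 4 + 4 + 4 | 20 | met | 20 | met |

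The stated rule can be met with 1 active day in the week. With credit up to 4 per day it needs at least 4, since 14/4 = 3.5.

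**3. Carry this to one participant.**
- *Feasibility criterion:* 14 bouts on one day in each of 8 weeks is enough. That is 8 active days against 5 × 12 = 60 prescribed days.
- *Adherence total, 7 + 7 in all 12 weeks:* 14 × 12 = 168, and 168/240 = 70% exactly. High adherence is above 70%, so this pattern meets every week but is not high.
- *Adherence total, high band:* this needs 169 bouts. At 4 a day that takes at least 43 days (169/4 = 42.25); at 20 a day it takes 9 (169/20 = 8.45). The band cannot tell these apart.

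**4. What it could do to the trial-level verdict (illustration only).** More than 70% means at least 29 of 40 (one arm) or 57 of 80 (both arms). Let s be the share who meet the criterion with spread-out bouts and b the further share who meet it only by massing. The documents give neither; both are assumptions. The chance of passing is P(X ≥ 29 or 57), with X ~ Binomial(n, s + b).

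| n | s | b = 0 | b = 5% | b = 10% | b = 20% |
|---|---|---|---|---|---|
| 40 | 55% | 0.018 | 0.071 | 0.205 | 0.715 |
| 40 | 60% | 0.071 | 0.205 | 0.441 | 0.912 |
| 40 | 65% | 0.205 | 0.441 | 0.715 | 0.988 |
| 80 | 55% | 0.002 | 0.025 | 0.145 | 0.818 |
| 80 | 60% | 0.025 | 0.145 | 0.458 | 0.978 |
| 80 | 65% | 0.145 | 0.458 | 0.818 | 1.000 |

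If massing is absent, nothing changes. If the true share is somewhat below 70%, a massing share of 10% to 20% can move the verdict a long way.

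**The case against.** The other side has real arguments.

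- **The dose is also stated weekly.** Interventions gives a weekly minimum, and the limitations paragraph of the Discussion gives at least 20 bouts per week. A weekly count is thus a recognised form of the prescription. This stands, and it is why the stated count should stay as the main figure.
- **Four a day is a minimum.** A week of 5 + 5 + 5 well-spaced bouts is credited 12 and fails, although each active day met the daily instruction. This stands as a limit of the credited figure.
- **A daily limit does not detect bunching within a day.** Four bouts back to back on 4 days are credited 16 and pass. This stands; only time stamps would show it.
- **It is late.** By March 31, 2026, 65 of the planned 80 participants were enrolled, and the analysis plan was posted on April 30, 2026. Replacing the main rule now is debatable, and a new survey question cannot recover days for weeks already reported.
- **Conduct discourages massing.** Reminders are daily, days and times are chosen at onboarding, and the calls at weeks 1 and 2 compare adherence with the prescription. This makes extreme patterns less likely but does not change the scoring.
- **The analysis plan is not shown.** It may already summarise active days. However, the article itself fixes the adherence measure and the feasibility rule, so the point concerns stated definitions and not an omission.

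A reader might go further and infer that massing will occur and the feasibility result will be wrong. Nothing in the documents says how common massing will be. A reader might also infer that one or two sessions in the whole trial would suffice. They would not, because at least 8 separate weeks must each reach 14 bouts.

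**Conclusion.** The concern holds as a limit on what the feasibility rule can show. As stated, the rule can be met on 1 or 2 days a week, and the adherence total can be built up without regard to days, while the prescription and the definition of the intervention depend on spread. The only numerical feasibility threshold therefore cannot separate the tested format from massed sessions of the same volume. This follows from the text and the arithmetic alone.

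The effect on the actual result cannot be sized: it depends on the share of participants who mass bouts, which could be nil or material. The documents do not support calling the weekly count an error or requiring its replacement. They support a prespecified day-based result beside it, with a conclusion that depends on both.

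**What to change.** Leave the stated, uncapped count and rule as the main figure. By dated amendment of the analysis plan, before analysis starts, prespecify by arm, from the app's daily log:

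1. active days per week, and days per week with at least 4 bouts;
2. the same feasibility rule (at least 14 bouts in at least 8 of 12 weeks, by more than 70% of participants) applied to bouts credited up to 4 per day.

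Show survey-only bouts whose day is unknown separately. State in advance that feasibility of the spread-out format will be claimed only if the day-based result supports it, and that otherwise only the weekly volume will be described as feasible. If the posted plan already contains the day-level summaries, only the credited rule and this reading need adding. The change concerns scoring alone and leaves what participants are asked to do untouched.

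There is still time: analysis begins only after all enrolled participants have finished, and no interim analysis is planned. The fix assumes that the app log keeps the date of each bout.

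The costs are a little more analysis, a possibly less favourable figure, and no credit in the supportive figure for spaced bouts above 4 on a day. Back-to-back bouts within a day stay undetected unless the app keeps time stamps.
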